### Perioperative period (up until discharge)

Delirium and pain are assessed postoperatively in the afternoon/evening while patients are in the hospital. Daily delirium assessments collected specifically for the ENGAGES-Canada study are entered into the Washington University School of Medicine Research Electronic Data Capture (REDCap)
^
40
^ database. EEG data, including BIS values, WAVcns, PSi values, and duration of EEG burst suppression are collected in both the guided as well as in the usual care group. In the usual care group, anesthesiologists are blinded to EEG data
^
23,
41
^. Perioperative data, including the repeated measures data, are saved for analysis from the intraoperative electronic data capture. As part of the routine data collection, we obtain for each patient a detailed medical history, surgical history, specific risk factors, medications, Blessed Dementia rating scale, screening for sleep apnea, laboratory values, medications during surgery, physiological readings, and parameters from the postoperative recovery period. At the time of discharge, patients will also complete a measure of immediate stress reactions (13-item Peritraumatic Distress Inventory; PDI) and peritraumatic dissociation (10-item Peritraumatic Dissociative Experiences Questionnaire; PDEQ) in the perioperative period, which have been found to be strong predictors of incident psychiatric disorders immediately following the stressful experience. Furthermore, they will complete an adapted 4-item PHQ-4 concerning more general anxiety and depressive symptoms, specifically during the perioperative period. These tests take patients approximately 5 minutes in addition to their CAM long form assessment (10 minutes).

### Postoperative delirium

The primary outcome of the study is the incidence of postoperative delirium. Assessment of postoperative delirium is conducted in patients that can be sufficiently aroused according to a Richmond Agitation and Sedation Score ≥ -3. Assessment of patients for delirium is performed from day one to day 5, once daily, in the afternoon/evening. A diagnosis of delirium for each patient is based on an approach combining a standardized daily assessment with a structured chart review. Members of the research team who are blinded to the treatment arm of the study assess patients for delirium using the Confusion Assessment Method (CAM long form)
^
42
^, or the Confusion Assessment Method for the Intensive Care Unit (CAM-ICU)
^
43,
44
^ for patients who are unable to speak (e.g., have a tracheal tube or tracheostomy). The CAM long form is deemed a viable tool that can be used by non-psychiatrists and by non-mental health professionals for delirium detection
^
42
^. The CAM long form has subsequently been validated in a number of studies and against a reference standard, with a sensitivity of >94% and a specificity of >89%
^
45
^. The CAM long form and the CAM-ICU are reliable instruments in good agreement with the DSM-IV criteria for delirium
^
44,
46,
47
^. To complete the delirium assessment of patients, a trained clinical researcher blinded to the CAM results and group assignment conducts a structured chart reviews for delirium detection. A positive CAM long form, or CAM-ICU, or chart review delirium detection
^
48,
49
^ is deemed sufficient and necessary to diagnose incident delirium in the ENGAGES-Canada trial. The approach combining a CAM long form interview, or a CAM-ICU, plus a chart review results in an increase in the sensitivity while retaining specificity in detecting incident delirium
^
48,
49
^. In addition, use of a chart review bolsters the pragmatic aspects of this trial, since it obtains information from a readily available source. Determination of delirium severity is based on the CAM-S long form measure or the CAM-ICU-7 Delirium severity instrument
^
50,
51
^.

The CAM long form assessment that is used in the trial was developed by [name] and colleagues
^
42
^, and includes a brief cognitive battery. All study team members who perform delirium assessments undergo a structured training process. For the initial training, representatives from the research team participated in a full-day training program led by [name], the original creator of the CAM long form
^
52
^. Those who attended this initial training are overseeing the training of other team members. Trainees must demonstrate competence at both conducting CAM long form and CAM-ICU interviews and in scoring these interviews. To establish their ability to score CAM long form interviews, trainees accompany trained team members to conduct CAM long form interviews. A trained member of the research team conducts each CAM long form interview for patients enrolled in the trial. The trainee observes the interview, but scores the CAM long form independently. The trainee must agree with the trainer on the presence or absence of all 12 cognitive features assessed by the CAM long form on a minimum of two delirious and two non-delirious patients. After meeting the stipulations of training, the newly trained team member will conduct their first interview of a patient enrolled into the trial in the presence of a previously trained team member. Independently of the training, all team members who are participating in CAM long form assessments must view and rate nine videos of standard interviews of actors depicting delirious and non-delirious patients. Research team members must be trained on CAM long form assessments prior to completing any structured delirium chart reviews.

This structured process is employed to evaluate and confirm the quality of the assessments of delirium. In all cases the assessments of delirium are reviewed within three days by a fellow member of the research team to evaluate internal consistency of scoring and completeness. Once a month, all challenging delirium assessments are discussed in a conference call including investigators from all sites. Whenever there is ongoing disagreement regarding a CAM long form, CAM-ICU or delirium chart review, these are allocated to experts for adjudication (involving [name]). Ongoing interrater-reliability assessments of all study staff are planned annually. A random selection of CAM long form, CAM-ICU, and structured chart reviews are sent to experts for quality control purposes.

### 30-days postoperative

Self-report psychiatric and cognitive symptom measures are either mailed to patients 30-days post-surgery with a stamped and addressed return envelope, sent by e-mail, or obtained through a telephone call. The following measures are re-administered: Falls Questionnaire, AUDIT-C, PDEQ, PCL-5, PHQ-4, PROMIS Global Health, PROMIS Applied Cognition-General Concerns, and PROMIS Applied Cognition-Cognitive Abilities. These tests take approximately 15 minutes for patients to complete.

### 1-year postoperative

Self-report psychiatric and cognitive symptom measures are either mailed to patients 1-year post-surgery with a stamped and addressed return envelope, sent by e-mail, or obtained through a telephone call. The following measures are re-administered: Falls Questionnaire, AUDIT-C, PCL-5, PHQ-4, PROMIS Global Health, PROMIS Applied Cognition-General Concerns, and PROMIS Applied Cognition-Cognitive Abilities. Additionally, patients are contacted via phone and receive the Short Blessed Test. These tests take patients approximately 15 minutes to complete by writing. The phone call for the Short Blessed Test lasts approximately 3 minutes.

### Sample size calculation statistical analyses

Based on previous studies in cardiac surgery patients, we conservatively estimated a delirium incidence in the control group of 25%
^
2–
9
^ and based on meta-analyses of randomized trials we estimated a relative reduction in delirium with guidance of anesthesia based on EEG waveform of more than one-third
^
3,
7,
24
^. Assuming a two-sided alpha <0.05 and 1200 patients, we estimated >90% power to be able to detect an absolute decrease in the incidence of delirium of 8%
^
27
^. With a more stringent two-sided alpha <0.005, we estimated >70% power. We anticipate that most patients will be available for primary outcome ascertainment (i.e. incident postoperative delirium assessment). Continuous variables will be presented as mean (SD) or median (interquartile range [IQR]), depending on their distributions. Chi-square or Fisher’s exact tests will be used for comparisons of discrete data. Unpaired Student’s t or Mann–Whitney U tests will be used for comparisons of continuous data, depending on their distributions. Confidence intervals for median differences will be calculated using Hodges-Lehmann estimates, and for differences between proportions we will use Newcombe’s method with continuity correction
^
53
^. For the primary outcome, the proportion of patients with incident postoperative delirium will be compared between the two study groups. We will conduct three post-hoc sensitivity analyses to assess whether improved clinician fidelity to the guided protocol might alter the primary outcome. Within the guided group 25% of cases will be excluded with the (1) longest cumulative electroencephalogram suppression time; (2) longest cumulative time with BIS, WAVcns <40 or PSi <25; and (3) highest median volatile anesthetic concentrations. To compare time to delirium onset between groups, we will construct Kaplan-Meier curves for each group and conduct a log-rank test. We will perform a covariate adjustment including likely risk factors for delirium (including age, sex, history of depression, history of delirium, AD* Test, Short Blessed Test, comorbidity index, and study center) using two methods: (1) logistic regression and (2) standardized estimator combined with bootstrapped 95% confidence intervals (CIs)
^
54
^. We will compare delirium incidence between groups, segregated by Charlson Comorbidity Index categories
^
55
^. Patients will be assessed based on their randomization group in accordance with an intention-to-treat approach. We will also conduct a per protocol sensitivity analysis: when clinicians in the usual care group view EEG data, these patients will be included in the guided group; and where there are technical difficulties in viewing electroencephalogram data in the guided group, these patients will be included in the blinded group. Patients who cannot be assessed for delirium will be excluded from the primary outcome analysis. In two sensitivity analyses, these patients (unless they die during surgery) will either all be assumed to have had incident delirium or not to have had incident delirium. We will compare preoperative characteristics between respondents and alive non-respondents to 30-day postoperative surveys. We will do the same for the 1-year postoperative surveys. Results will be presented with 95% CIs. All significance testing will be two-sided, with P values <0.05 considered as providing suggestive evidence and P values <0.005 as providing more compelling evidence
^
56
^. The statistical analyses will be performed with
SAS, V.9.4 (SAS Institute, Cary, North Carolina) and/or
STATA, V.14.2 (StataCorp LP, College Station, Texas).

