### The ENGAGES-Canada study: potential impact

The intent of the ENGAGES-Canada study is to determine if EEG-guided anesthesia to reduce anesthetic agent administration, thereby minimizing episodes and durations of EEG suppression, can effectively decrease the incidence of POD and its downstream sequelae in patients undergoing cardiac surgery (
Table 1). The approach of minimizing periods of EEG suppression specifically during cardiac anesthesia has not been previously tested in a large clinical trial. Recently published meta-analyses have suggested that EEG guidance of anesthesia decreases the incidence of POD by more than a third
^
25
^. If this result is reproduced in subsequent rigorous clinical trials, it will have important implications for how anesthesia is administered – especially to older adults. On the other hand, premature implementation based on the existing preliminary evidence might have unintended negative consequences. It is within this context that the ENGAGES trial and ENGAGES-Canada will provide critically clarifying information
^
27,
28
^. The ENGAGES trial addressed the question in unselected older adults undergoing major surgery
^
26
^. ENGAGES-Canada will address the question specifically in cardiac surgery patients, where the risk of POD is especially high
^
2–
9
^.

**Table 1. T1:** ENGAGES-Canada: Conceptualization – Intervention, Mediators, Outcomes, and Adverse Events. Assessment acronyms: EEG – Electroencephalogram; ICU – Intensive Care Unit.

ENGAGES-Canada: Conceptualization	
Intervention	· **EEG-guided reduction of anesthesia**
Mediators • Hypothetically linked both to the intervention as well as to the outcomes and the adverse events	·Intraoperative mediators ○Decrease in **EEG suppression** ○Decrease in anesthetic exposure ○Decrease in hypotension
Primary Outcome	· **Incident postoperative delirium**
Exploratory Secondary Outcomes	·Length hospital and ICU of stay
Other Exploratory Outcomes	·Postoperative **falls** incidence and association between delirium and falls ·Delirium duration and severity ·Postoperative **quality of life** ·Perioperative distress and dissociation ·Other delirium outcomes: delirium on day 0, time to delirium onset, sensitivity analyses, covariate adjustment · intraoperative mediating events: anesthetic concentrations, electroencephalogram suppression time and hypotension duration ·Functionality ·Cognition

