Major Perioperative Adverse Events	·Undesirable movement ·Awareness with recall ·Serious complications (examples: major blood loss and transfusions, stroke, sternal wound infection, sepsis, dialysis, prolonged intubation) ·Death

Thus, the objective of the ENGAGES-Canada trial is to address whether reducing anesthetic administration based on EEG information during cardiac surgery primarily decreases the incidence of POD, and secondarily decreases the duration and severity of POD. Other relevant measures in the trial will be clinically relevant outcomes determined at the index hospitalization, at approximately 30-day postoperatively, and at approximately 1-year postoperatively.

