## Methods

### Overview of the research design and study subjects

The Research Ethics Boards of the Montreal Heart Institute (2017-2164), the University of Manitoba (HS18290), Kingston University (ANAE-298-16), and the University of Toronto (17-5933) all approved the study. The details of the design of the ENGAGES-Canada study are included in this protocol and it contains the complete list of elements from the SPIRIT (Standard Protocol Items: Recommendations for Interventional Trials) checklist
^
29,
30
^. This study was registered with ClinicalTrials.gov (
NCT02692300) on 26 February 2016.

 The ENGAGES-Canada will randomize 1200 patients of 60 years old and older in a clinical trial designed to be pragmatic. The first patient randomized in the trial was enrolled in November 2016. Competent patients who provide informed consent and who are undergoing elective cardiac surgery with cardiopulmonary bypass are eligible to be included in the study. There are no absolute contraindications to EEG monitoring, and the design of the ENGAGES-Canada trial is largely pragmatic. Exclusion criteria include positive preoperative delirium screening. In addition, patients with hearing impairment, and those who are blind, illiterate, or do not speak French or English will be excluded because they will not be able to participate adequately in delirium screening. Finally, patients who have previously had general anesthesia and who have reported experiencing intraoperative awareness will also be excluded
^
31
^.

Participants are randomized to either one of two groups: in the guided group, anesthetic administration is guided largely by EEG waveform; in the other group, patients receive current usual anesthetic care for cardiac surgery. Delirium and other assessments take place preoperatively, and delirium is assessed postoperatively from day one to five while the patient is in the hospital. The primary outcome will be the incidence of postoperative delirium. As secondary and other outcomes, we will also examine stress reaction and dissociation at discharge as potential factors associated with delirium and predictors of postoperative psychiatric symptoms. At 30-days and at 1-year, follow-up assessments include the quality of life as related to health, cognitive functioning, and information on psychiatric symptoms and on the incidence of falls – collected via self-report.

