### Outcomes

The primary outcome is the occurrence of incident delirium on postoperative days 1-5. Secondary outcomes include: length of ICU and hospital stay; duration and severity of delirium POD 1-5; incidence of falls and association between delirium and falls at 30 days and at 1 year; association between delirium and quality of life by PROMIS Global Health; predictors of Post-Traumatic Stress Disorder (PTSD) by PDEQ at 5 days and 30 days postoperatively; and predictors of Post-Traumatic Stress Disorder (PTSD) by PDEQ at 5 days and 30 days postoperatively. Exploratory outcomes include co-variates of delirium, functionality, and cognitive impairment at 30 days and at 1 year postoperatively. Pre-specified exploratory analyses include intraoperative mediating events such as anesthetic concentrations, electroencephalogram suppression time, and hypotension duration. Perioperative adverse events include undesirable intraoperative movement, awareness with recall, complications such as major blood loss and transfusions, stroke, sternal wound infection, sepsis, dialysis, prolonged intubation, and mortality rates at 30-day and at 1-year.

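### The generic median and Hodges-Lehmann rule does not suit delirium duration: applied to all patients it gives 0 (0 to 0) at the protocol's own delirium rates, and duration is ranked inconsistently

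*Protocol article*

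**What the plan says.** In the Protocol article, the section on sample size and statistical analyses handles all continuous variables together. They are summarised by mean or median and tested by t test or Mann-Whitney, according to the shape of the data. For medians, "Confidence intervals for median differences will be calculated using Hodges-Lehmann estimates". The same section commits to analysis by randomised group and to 95% intervals. It assigns neither a summary measure nor an analysis set to delirium duration. The section on secondary outcomes adds multivariable regressions without saying which outcome gets which model.

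Duration is prominent. The stated objective is that guidance lowers incidence and "secondarily decreases the duration and severity of POD". The Outcomes section lists as secondary "length of ICU and hospital stay; duration and severity of delirium POD 1-5", and the Abstract agrees. Table 1 instead puts "Delirium duration and severity" under its heading for other exploratory outcomes and keeps only length of stay at the secondary level.

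On the measurement window, "delirium is assessed postoperatively from day one to five while the patient is in the hospital".

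**The concern.** A count of delirium days over days 1 to 5 has a large block of zeros, one for each patient who never becomes delirious. Anyone choosing by the shape of the data would call it skewed and take the median branch. The Hodges-Lehmann estimate is the median of all between-arm pairwise differences. If most pairs tie at zero, that median and its interval are zero and carry no information about the size of the effect.

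The trial could then report a significant rank test for part of its second objective beside a difference of 0 (95% interval 0 to 0). A reader could take that as a precise finding of no effect on duration. The obvious escape, analysing only delirious patients, gives up the randomised comparison, because delirium is the outcome that the intervention is meant to change.

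**Working it through.** **Inputs from the documents**
- Control incidence: "we conservatively estimated a delirium incidence in the control group of 25" (per cent).
- Effect: "an absolute decrease in the incidence of delirium of 8" (percentage points), so 17% in the guided arm.
- 1200 patients allocated 1:1, so 600 per arm.

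**The plan's own figure first.** A two-proportion test of 25% against 17% with 600 per arm has power 92.6% at two-sided 0.05 and 72.5% at 0.005. Both agree with the stated bounds of more than 90% and more than 70%.

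**Share with zero days**
- Control: 0.75 × 600 = 450. Guided: 0.83 × 600 = 498.
- Overall: (450 + 498) / 1200 = 79%.

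**Between-arm pairs**, 600 × 600 = 360,000, difference = guided minus control
- Both zero: 450 × 498 = 224,100, which is 0.75 × 0.83 = 62.25%.
- A negative difference needs a delirious control patient: at most 25% of pairs.
- A positive difference needs a delirious guided patient: at most 17% of pairs.
- In sorted order, zeros therefore fill at least the stretch from the 25% point to the 83% point.

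**Where the estimate and limits fall**
- The estimate is at the 50% point.
- The 95% limits, from inverting the Mann-Whitney test, are at 0.5 ± 1.96 × √(360,000 × 1201 / 12) / 360,000 = 0.5 ± 0.0327, that is, about 46.7% and 53.3%.
- All three points lie inside the block of zeros, so the result is 0 (0 to 0). The lengths of the delirious episodes do not enter the argument.
- By the same bounds, the collapse is certain whenever both arms have a delirium incidence below about 46.7%.

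**Simulation.** There were 100 trials per scenario, with 600 per arm. Episode lengths of 1 to 5 days were assumed, either short-skewed (probabilities 0.50, 0.25, 0.13, 0.07, 0.05) or flat (0.20 each), with the same distribution in both arms. The row at 25% uses 17% in the guided arm; the others use a one-third relative reduction.

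| Control incidence | Estimate = 0 | Interval = 0 to 0 |
|---|---|---|
| 25% | 100% | 100% |
| 20%, 35%, 45%, 50% | 100% | 100% |
| 60% | 100% | 71% to 92% |
| 70% | 44% to 84% | 0% to 13% |

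At 25% against 17%, Mann-Whitney gave p < 0.05 in 91% (short) and 95% (flat) of the same trials.

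**What a mean difference would show, under the same assumptions**
- Short: mean episode 0.50 + 0.50 + 0.39 + 0.28 + 0.25 = 1.92 days. Expected difference (0.25 − 0.17) × 1.92 = 0.15 days per patient.
- Flat: mean episode 3 days. Expected difference 0.08 × 3 = 0.24 days per patient.

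**Delirious patients only** (150 against 102, 300 simulated trials). With flat durations in controls and short ones in the guided arm, the estimate was −1 or −2 days in every trial. With identical distributions it was 0 in every trial. The collapse is avoided, but the two groups compared are no longer the randomised groups.

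**The case against.** The strongest reply is that the article never assigns Hodges-Lehmann to duration. The rule is generic, it also allows means with a t test, and regressions are mentioned for secondary outcomes. No analysis set is named. The collapse needs two choices that the text leaves open: all patients, and a median summary. An analysis plan that is not shown may settle both. Even on that branch the planned rank test works, so what fails is one interval for one non-primary outcome. All of this stands. A reader might infer that the trial will report exactly zero, or that it cannot estimate its effect on duration. The documents support neither.

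The reply does not remove the point. Neither the t test nor the regressions are tied to duration, and choosing by the shape of the data leads to the branch that fails. Analysis by randomised group is stated, which points to all patients.

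A reader might also extend the criticism to time to onset ("we will construct Kaplan-Meier curves for each group and conduct a log-rank test") and to length of stay, and say that both ignore death and discharge. The documents do not say so. They are silent on censoring and on how in-hospital deaths enter length of stay, and a condensed article commonly leaves such detail to the full plan. Any bias figure would rest on assumed discharge and delirium hazards, because the documents give none.

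**Conclusion.** The point holds in conditional form. If duration is compared by randomised group in all patients under the stated median rule, the estimate and 95% interval are 0 (0 to 0) at 25% against 17%. This follows from arithmetic and needs no assumption about episode length. It holds for certain while incidence in both arms is below about 46.7%, and in the simulations it held up to a control incidence of 50%. It weakens only towards the top of the 20% to 70% range quoted in the Background. The Study status section reports total delirium incidence in line with the planning value, so the collapse would be the ordinary case on this branch.

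The simulated Mann-Whitney rates and the expected mean differences of 0.15 and 0.24 days do rest on assumed episode lengths.

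Separately, and without any condition, the article contradicts itself on rank: duration and severity are secondary in the objective, the Outcomes section and the Abstract, but other exploratory in Table 1.

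The primary outcome, its test and the sample size are untouched.

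**What to change.** For delirium duration:
- Name all randomised, assessable patients as the analysis set, by randomised group.
- Replace the Hodges-Lehmann interval with the difference in mean delirium days over days 1 to 5 and a bootstrap 95% interval. A rank-based probability or win odds would also serve. Keep Mann-Whitney as the test.
- Label any summary restricted to delirious patients as descriptive.
- State how in-hospital deaths and days after discharge are counted, since assessment stops at discharge and a mean over five days needs a value for each.

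Make Table 1 agree with the objective and the Outcomes section on the rank of duration and severity.

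The cost is a few sentences and modest programming, with no new data collection. There are two drawbacks. The mean difference will be a small fraction of a day and needs a sentence of explanation. The rule for unassessed days is an assumption that should be stated openly.

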## Data collection

### Preoperative

Preoperative assessments are performed in the Pre-Anesthesia Clinic or hospital ward. These include demographic information and medical history, assessment of preoperative quality of life, psychiatric symptoms (i.e., anxiety, depression, alcohol use, trauma history, and posttraumatic stress disorder), objective and subjective cognitive functioning measures
^
35,
36
^, and evaluation of falls’ history. The purpose of the preoperative assessments is to identify cognitive and psychiatric disorders in order to better understand risk factors for postoperative delirium and its sequelae. For example, postoperative delirium has been associated with impaired performance on preoperative cognitive tests
^
37
^, and postoperative delirium predicts persistent postoperative cognitive decline
^
6
^. These known risk factors will be included in covariate analysis for the primary outcome and will be used in exploratory analyses. The following measures were selected for the assessment of cognitive and psychiatric symptoms based on their brevity, frequency of use in medical practice, validity for older adults, and lack of copyright restrictions: (1) 8-item AD8 Dementia Screen
^
38
^, (2) History of Delirium Screen, (3) Short Blessed Test
^
39
^, (4) 3-item Alcohol Use Disorders Identification Test (AUDIT-C), (5) 1-item surgical anxiety visual analogue scale, (6) Trauma History Screen, (7) Posttraumatic Stress Disorder Checklist (PCL-5; past-month PTSD assessment), (8) 4-item Primary Care PTSD Screen (PC-PTSD; lifetime PTSD assessment), (9) 4-item Patient Health Questionnaire (PHQ-4; anxiety and depressive symptoms), (10) 10-item Patient Reported Outcomes Measurement Information System (PROMIS) Global Health (physical and mental health related quality of life), (11) 4-item PROMIS Applied Cognition-Cognitive Concerns, (12) 4-item PROMIS Applied Cognition-Abilities (see extended data
^
32

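### The primary delirium comparison leaves planned covariate adjustment among the exploratory analyses; making the planned standardized estimator primary would add precision at little cost

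*Protocol article*

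**What the plan says.** All of this is in the protocol article.

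- **Primary comparison** (Sample size calculation statistical analyses): "For the primary outcome, the proportion of patients with incident postoperative delirium will be compared between the two study groups". The sentence does not itself call the comparison unadjusted. That follows from the same section, which assigns chi-square or Fisher's exact tests to discrete data and a continuity-corrected Newcombe interval to differences in proportions.
- **Adjustment** (same section): "We will perform a covariate adjustment including likely risk factors for delirium". The listed factors are age, sex, history of depression, history of delirium, the AD test (presumably the AD8), the Short Blessed Test, a comorbidity index and study centre. Two methods are named: logistic regression, and a standardized estimator with a bootstrap 95% interval.
- **Rank of the adjustment**: Table 1 lists covariate adjustment in the row for other exploratory outcomes, beside the sensitivity analyses.
- **Source of the covariates** (Preoperative), on the baseline cognitive and psychiatric measures: "These known risk factors will be included in covariate analysis for the primary outcome".
- **Power**: "we conservatively estimated a delirium incidence in the control group of 25" per cent. "Assuming a two-sided alpha <0.05 and 1200 patients", the authors write, "we estimated >90% power to be able to detect an absolute decrease in the incidence of delirium of 8" percentage points. They add: "With a more stringent two-sided alpha <0.005, we estimated >70% power".

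**The concern.** The trial collects baseline factors that it regards as linked to delirium, and it already plans an estimator that turns them into precision for the risk difference. It then leaves that estimator out of the main result. Standardization averages model-based risks over the trial population, so it targets the same marginal risk difference as the simple comparison, usually with a smaller variance.

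The loss matters most at the 0.005 level, which the protocol reserves for more compelling evidence and where it claims only just over 70% power. At 0.05, power is already near 93% and there is little left to gain.

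**Working it through.** **Inputs.** Control risk 25%, an absolute decrease of 8 points (so 17% under guidance), 1200 patients and two-sided alpha of 0.05 and 0.005 come from the sample-size section. Allocation of 1:1 (600 per arm) comes from Randomization and blinding. All patients are taken as assessable, because no loss rate is given. No AUC or R² for the covariates is stated, so prognostic strength is an assumption shown as a range.

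**Step 1: reproduce the stated power.**

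- Unpooled variance: 0.25×0.75/600 + 0.17×0.83/600 = 0.0003125 + 0.0002352 = 0.0005477, so SE = 0.02340.
- Pooled null SE: √(2×0.21×0.79/600) = 0.02352.
- Power (pooled null) = Φ[(0.08 − z×0.02352)/0.02340]. With z = 1.960 this is 92.6%; with z = 2.807 it is 72.5%.
- Using the unpooled SE throughout gives 92.8% and 73.0%. A continuity correction gives 91.6% and 70.1%.

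All variants agree with the stated figures of more than 90% and more than 70%.

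**Step 2: variance of the standardized risk difference.** Let X be a standard-normal prognostic score with logistic slope s. The intercepts are set so that the marginal risks stay at 25% and 17%. With individual risks p0(X) and p1(X):

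V = E[p0(1−p0)]/600 + E[p1(1−p1)]/600 + Var(p1−p0)/1200

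| Slope s | AUC | E[p0(1−p0)] | E[p1(1−p1)] | Var(p1−p0) | V | Variance reduction |
|---|---|---|---|---|---|---|
| 0.5 | 0.64 | 0.1793 | 0.1362 | 0.0005 | 0.000526 | 3.9% |
| 0.75 | 0.69 | 0.1703 | 0.1306 | 0.0009 | 0.000502 | 8.3% |
| 1.0 | 0.74 | 0.1599 | 0.1236 | 0.0014 | 0.000474 | 13.5% |

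**Step 3: convert to patients and power.** Equivalent N = 1200 × 0.0005477/V. Power = Φ(0.08/√V − z), to be compared with the unpooled 92.8% and 73.0%.

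| Slope s | Equivalent N | Extra patients | Power at 0.05 | Power at 0.005 |
|---|---|---|---|---|
| 0.5 | 1249 | 49 | 93.7% | 75.2% |
| 0.75 | 1308 | 108 | 94.6% | 77.7% |
| 1.0 | 1387 | 187 | 95.7% | 80.7% |

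**Step 4: simulation check.** There were 4000 trials per scenario, with 1200 patients and 11 baseline covariates. The estimator was the logistic standardized risk difference, with an influence-function SE in place of the planned bootstrap.

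- Covariates with R² 6% (AUC 0.66): power at 0.005 rose from 72.4% to 75.7%, and at 0.05 from 92.3% to 93.8%.
- Covariates with R² 12% (AUC 0.72): power rose from 72.7% to 79.7%, and from 92.3% to 95.5%.
- The mean estimate stayed at −0.080 in these scenarios, so the target is unchanged.
- Type I error at R² 12% was 5.3% and 0.43%, near nominal.
- Uninformative covariates: variance ratio 1.006, and power at 0.05 of 93.3% either way.

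**The case against.** The strongest reply is that nothing here is wrong. An unadjusted comparison of proportions is a valid intention-to-treat analysis, it needs no model and no rule for missing baseline questionnaires, and the stated power is right. The adjusted result will be reported anyway. The gain depends on a prognostic strength that the documents do not give, and at 0.05 it is only about 1 to 3 points. The 0.005 level is a grade of evidence, not a pass/fail threshold. All of this stands, and it limits the point to an improvement.

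The cost is also not quite zero. The covariate list is introduced as examples and is therefore open, and the model form and the handling of missing covariates would have to be fixed. Study status reports interim analyses at 240 and 570 patients. The article says randomization remains blinded, but this would still be a mid-trial change to the primary analysis and needs documenting as one.

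A reader might infer four stronger criticisms that the text does not support:

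- **That the predictors are strong.** The article calls them only likely or known risk factors and gives no measure of strength.
- **That adjusted and unadjusted results compete without precedence.** Table 1 ranks the adjustment below the primary comparison. Only the order of the two adjusted methods is open.
- **That the planned test and interval conflict.** With 150/600 control events and 115 to 126 guided events, they disagree at 0.05 at one count only, and only if the uncorrected chi-square is used.
- **That the comorbidity subgroup plan is deficient.** The article says: "We will compare delirium incidence between groups, segregated by Charlson Comorbidity Index categories". Whether an interaction test accompanies this is separate from the primary analysis and may be settled in an analysis plan that is not shown.

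**Conclusion.** The point holds as a missed efficiency. The main result is planned without adjustment, while a more precise estimator of the same risk difference, built on data already collected, sits among the exploratory analyses. Neither the validity of the planned test nor the power statement is in question.

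The size of the gain rests on three assumptions: a baseline score with logistic slope between 0.5 and 1.0, the design risks of 25% and 17%, and complete ascertainment. Weaker covariates would yield less than this range, and uninformative ones essentially nothing either way. The practical benefit lies mainly at 0.005, where the gain is about 2 to 8 points.

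**What to change.** Before unblinding, by a documented change made blind to allocation:

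1. Name the standardized (g-computation) risk difference as the single primary analysis, taken from a logistic model with treatment, the listed covariates and centre. Report it with its bootstrap interval and a p value from the same procedure.
2. Close the covariate list, state the form in which each covariate enters, and fix one rule for missing baseline values.
3. Keep the unadjusted comparison as supportive. Report the logistic odds ratio as secondary, since it is a conditional measure and not the risk difference used for the power calculation.

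No new patients, data or estimation method are needed. The cost is a short amendment to the analysis section and the work of fixing the covariate list, model form and missing-value rule in advance.
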